### 5.4 Secondary study parameter(s)

- In equivalent analyses as mentioned above (6.4. *primary study parameters*), we will examine the effect of the intervention on the secondary study parameters (i.e. Quality of Life, general and positive symptomatology, depression, inhibition/ activation, need for care and overall functioning).

- Cost effectiveness and Budget impact Analyses:

#### Cost Effectiveness Analysis (CEA):

The economic evaluation will be conducted as a cost-effectiveness analysis, CEA, with costs / treatment responder, and a cost-utility analysis, CUA, using quality adjusted life years (EQ-

5D/QALYs) as a generic measure of health gains. Both the CEA and the CUA will be conducted from the societal perspective and in agreement with the intention to treat principle. The trial's follow-up measurements do not exceed the time horizon of one year and therefore neither costs nor effects will be discounted. Sensitivity analyses will be directed at uncertainty in the main cost-drivers.

### Cost analysis

We will consider four types of costs: (1) the costs of offering the intervention, (2) costs stemming from health care uptake including the costs of medication, (3) patients' out-of-pocket costs, (4) costs stemming from productivity losses due to absenteeism and lesser efficiency while at work and owing to changes in the contractual number of work hours per week. The first two types of costs are also known as the direct medical costs and these will be based on the full economic costs of offering the interventions. For this we shall make use of the pertinent Dutch guideline for economic evaluation [18], and rely on the standard cost prices reported therein. The patients' out-of-pocket costs are known as direct non-medical costs and encompass the patients' costs of travelling to health services and parking costs incurred in the context of health care uptake. Finally, productivity losses will be based on the gender and age specific friction costs, as outlined in the Dutch guideline for costing. Data on resource use (health care uptake) and productivity losses will be collected with the latest version of the Trimbos/iMTA Questionnaire Costs associated with Psychiatric illness, TiC-P, [19]. The TiC-P is the most widely used health service receipt interview for economic evaluations in the Netherlands.

### CEA and CUA

The economic evaluation will be conducted alongside the randomised trial. The central clinical end-term will be treatment response, defined as an increase on the PANSS negative symptom score (with a 5-point increase meaning a clinically relevant change), for the CEA. For the CUA, the Dutch tariffs (utility weights) of the EQ-5D will be used for computing the QALYs [20]. The incremental cost-effectiveness ratio (ICER) will be computed to obtain the costs per treatment response and the costs per QALY gained. Stochastic uncertainty will be handled using 2,500 non-parametric bootstraps and plotting the simulated ICERs on the ICER plane. For decision-making purposes, the ICER acceptability curve will be plotted for various willingness-to-pay (WTP) ceilings for making judgements whether the adjuvant intervention offers good value for money relative to routine medical care alone. One-way sensitivity analyses directed at uncertainty in the main cost drivers will be performed to gauge the robustness of our findings across a range of likely values of those parameters.

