#### Anticipated Cost-Effectiveness/ Budget Impact

A secondary aim of the present study is to examine the cost-effectiveness of this new type of intervention. We based our estimated cost-effectiveness on the following calculation:

1. Costs of the intervention per patient are estimated at 800 Euro.
2. We expect a reduction in negative symptoms with an effect size of .66 compared to standard care only [3].
3. There is a small effect or no effect of usual care on negative symptoms [3&5]. Since the exact effect is unclear and our concern is the additional effect, we set the effect of usual care at 0, and use the effect of our intervention (effect size 0,66) compared to usual care. Assuming that negative symptoms resemble depression, and that negative symptoms persist half a year, this amounts to a QALY gain of  $0,66 \text{ (effect size)} \times 0,172 \text{ (conversion factor d->dw)} \times 0,5 \text{ (duration of half a year)} \text{ per patient} = 0.057$ .
4. The costs for an additional QALY then are  $800/0,057 = \text{€}14.035,09$  per additional QALY.
5. This is below the €20.000 cut-off, as a result of which the intervention may be considered costeffective

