### Hypotheses:

- 1) We hypothesize that CBT focused on social activation (CBTsa) will result in a substantial reduction in severity of negative symptoms, and in particular social withdrawal.
- 2) We expect this intervention to result in a reduction in need for care and QALY gain as a consequence of improvement in symptoms and social functioning.
- 3) We expect that CBTsa will lead to an improvement in terms of Quality of Life and overall functioning and symptomatology.

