### **2.2 Inclusion criteria**

In order to be eligible to participate in this study, a subject must meet all of the following criteria:

- (1) recent onset schizophrenia or related disorder (start antipsychotic medication <2 yr);
- (2) Social withdrawal (> 3 moderate severity on the PANSS N4; Passive/apathic social withdrawal; range 0-7);
- (3) Aged 18-35 years;
- (4) Fluent in Dutch
- (5) IQ>70;
- (6) Able and willing to give informed consent

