**Table 1. Test battery**

| Primary outcome          | Instruments                                                                                   | Characteristics Instrument                                                                                                                                                                                                                                                                                                                                                                                                                                                                                                                                    |
|--------------------------|-----------------------------------------------------------------------------------------------|---------------------------------------------------------------------------------------------------------------------------------------------------------------------------------------------------------------------------------------------------------------------------------------------------------------------------------------------------------------------------------------------------------------------------------------------------------------------------------------------------------------------------------------------------------------|
| Negative symptoms        | Negative symptom domain of the Positive and Negative Syndrome Scale (PANSS; Kay et al., 1986) | Consists of 7 item clusters and produces a total score ranging from 7 (minimum) to 49 (maximum).                                                                                                                                                                                                                                                                                                                                                                                                                                                              |

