## Patient outcome analysis (INBRA)

INBRA relies on the same data as CEA, but now we prefer to have a clinical outcome on a continuous measurement scale [24]. For this we will make use of the PANSS. INBRA is essentially a regression analysis where the treatment dummy, a prognostically relevant population characteristic (e.g. Dutch vs non-Dutch ethnicity) and their interaction are regressed on net-benefits. Net-benefits, NB, are defined as,  $NB = (E * \pi) - C$ , where E are effects (changes on the PANSS),  $\pi$  is an unknown quantity representing the willingness to pay (WTP) for one unit of health gain (decrease on the PANSS-negative) and C are the additional costs of offering the adjuvant CBTsa intervention. Because  $\pi$  is an unknown quantity, we will use a range of plausible WTP levels in our analysis. Within the regression framework, INBRA essentially evaluates the net-benefits as a function of the effect modification and thus helps to answer the question: who benefits most? – or more precisely, are there any subgroups in which the intervention is particularly cost-effective. This information may aid future improvements of the CBTsa intervention such that it may become more cost-effective in subgroups that now do not fully benefit from the intervention or else these data may guide decisions about referring those patients to the intervention such that these people may derive full benefit from the intervention in a cost-effective way.

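### The cost-effectiveness analysis defines treatment response as a 5-point increase on PANSS negative, so patients who deteriorate count as responders

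*Protocol*

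**What the plan says.** Protocol section 5.4, under CEA and CUA, sets the clinical outcome for the cost-effectiveness analysis. Treatment response is "defined as an increase on the PANSS negative symptom score (with a 5-point increase meaning a clinically relevant change"). The direction is given twice, once in the definition and once in the threshold. This response feeds one of the two planned incremental cost-effectiveness ratios (ICERs), the cost per responder. The other is the cost per QALY, based on EQ-5D.

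Elsewhere the protocol uses the same scale in the opposite direction:

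- Section 1, Hypotheses: CBTsa "will result in a substantial reduction in severity of negative symptoms".
- Anticipated Cost-Effectiveness/ Budget Impact: "We expect a reduction in negative symptoms with an effect size of .66 compared to standard care only".
- Section 5.4, Patient outcome analysis (INBRA): willingness to pay is attached to "one unit of health gain (decrease on the PANSS-negative").

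**The concern.** The responder rule is an operative definition, not background text. An analyst who programs it literally selects the patients whose negative symptoms grew by 5 points or more and reports the cost of producing one of them. If CBTsa works as hypothesised, fewer such patients should appear in the CBTsa arm. The incremental effect then becomes negative, and a helpful therapy that costs more would appear dominated by standard treatment. A harmful therapy would look beneficial.

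The error would carry through the 2,500 bootstrap replications into the ICER plane and the acceptability curve for that outcome. It would also leave two linked parts of one economic plan, the responder-based analysis and the net-benefit regression, scoring the same instrument in opposite directions.

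**Working it through.** **Step 1: which direction is worse?**

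- Table 1 lists the PANSS negative domain as the measure of negative symptoms. It "produces a total score ranging from 7 (minimum) to 49 (maximum").
- Section 2.2 admits patients with "Social withdrawal (> 3 moderate severity on the PANSS N4". A patient must score above a severity level to qualify, so higher means more severe.
- The hypothesis predicts a reduction in severity, and the INBRA section treats a decrease as gain.
- No section reverses the scoring or defines change as baseline minus follow-up, so nothing in the text makes an increase an improvement.

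The responder definition therefore contradicts the rest of the protocol. This conclusion needs no arithmetic.

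**Step 2: inputs for an illustration.** The protocol states no responder rate and no cost per responder, so there is no figure of its own to reproduce for this outcome. Its planning figure of EUR 14,035.09 per QALY does reproduce (800 / 0.057), but it does not depend on the responder rule.

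| Input | Value | Source |
|---|---|---|
| Effect size d | 0.66 | Anticipated Cost-Effectiveness/ Budget Impact |
| Mean change under ST, m0 | 0 ("we set the effect of usual care at 0"); -2 as a variant | same section; the variant is an assumption |
| Incremental cost | EUR 800 ("Costs of the intervention per patient are estimated at 800 Euro") | same section; using it as the whole cost difference is an assumption |
| SD of change, s | 4 to 8 points | assumption; not in the protocol |
| Shape | normal, same s in both arms | assumption |

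**Step 3: formulas.** Let change be follow-up minus baseline, with CBTsa mean m1 = m0 - 0.66 s.

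- Rule as written: P(change ≥ +5) = 1 - Φ((5 - m)/s)
- Direction reversed: P(change ≤ -5) = Φ((-5 - m)/s)
- Cost per responder = 800 / (CBTsa rate - ST rate)

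**Step 4: worked case, s = 6 and m0 = 0.** Here m1 = -0.66 × 6 = -3.96.

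- As written, CBTsa: 1 - Φ(8.96/6) = 0.068. ST: 1 - Φ(5/6) = 0.202. The difference is -0.135, and 800 / -0.135 is about -EUR 5,940.
- Reversed, CBTsa: Φ(-1.04/6) = 0.431. ST: Φ(-5/6) = 0.202. The difference is +0.229, and 800 / 0.229 is about +EUR 3,500.

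(Differences and costs use unrounded rates.)

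**Step 5: range over the assumptions.**

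| s | m0 | As written, CBTsa vs ST | Difference (points) | EUR per responder | Decrease ≥ 5, CBTsa vs ST | Difference (points) | EUR per responder |
|---|---|---|---|---|---|---|---|
| 4 | 0 | 2.8% vs 10.6% | -7.8 | -10,312 | 27.8% vs 10.6% | +17.2 | 4,653 |
| 4 | -2 | 0.8% vs 4.0% | -3.2 | -24,935 | 46.4% vs 22.7% | +23.8 | 3,368 |
| 5 | 0 | 4.8% vs 15.9% | -11.0 | -7,260 | 36.7% vs 15.9% | +20.8 | 3,841 |
| 6 | 0 | 6.8% vs 20.2% | -13.5 | -5,941 | 43.1% vs 20.2% | +22.9 | 3,495 |
| 6 | -2 | 3.4% vs 12.2% | -8.8 | -9,112 | 56.4% vs 30.9% | +25.5 | 3,137 |
| 8 | 0 | 9.9% vs 26.6% | -16.7 | -4,802 | 51.4% vs 26.6% | +24.8 | 3,226 |
| 8 | -2 | 6.2% vs 19.1% | -12.8 | -6,231 | 61.2% vs 35.4% | +25.8 | 3,097 |

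The written rule gives a negative difference in every case, and the reversed rule a positive one. The negative euro figures have no meaning as prices. They show only that the result has moved to the quadrant of higher cost and lower effect.

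**Step 6: where the reversal stops (s = 6, m0 = 0).**

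- d = 0.3: -7.4 points as written, +9.5 reversed.
- d = 0: both differences are 0.
- d = -0.3 (harm): +9.5 as written, -7.4 reversed.
- CBTsa SD 1.75 times the ST SD, CBTsa mean held at -3.96: -0.6 as written. At twice the ST SD: +2.5 as written.

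**The case against.** The strongest reply is that this is a slip of the pen. The outcome is called a response, the INBRA section has the direction right, and every statement of expectation speaks of reduction. The intended word was probably improvement, and a careful analyst would notice. That is likely true, but it does not dispose of the point. The protocol itself fixes this definition. An analysis that copies it is wrong, and one that silently reverses it departs from the written rule on a reported result.

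The second reply concerns reach, and it stands. Only the cost per responder is affected. The mixed-model primary analysis, the cost per QALY and the net-benefit regression do not use the responder rule, and cost-effectiveness is a secondary aim.

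The third concerns the consequence, and it stands as a set of conditions. The sign reverses if CBTsa shifts scores as hypothesised with similar spread in both arms. Appearing dominated also requires a higher cost under CBTsa. The analysis takes a societal perspective and includes productivity losses, so the cost difference could be negative. The ratio would still change sign, but CBTsa would then look cheaper and less effective, not dominated.

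Finally, the effect size of 0.66 comes from avolition-apathy in a chronic population. Applying it to an assumed SD of PANSS negative change is a convenience, so the percentages are illustrative only.

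**Conclusion.** The definition is wrong as written. It contradicts the protocol's own scale, hypothesis and net-benefit definition, and that conclusion rests on no numerical assumption.

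For size: with normal change, equal spread, d = 0.66, an SD of 4 to 8 points and mean change under ST of 0 or -2, the written rule gives CBTsa 3.2 to 16.7 percentage points fewer responders than ST. Counting decreases gives 17.2 to 25.8 points more. At an incremental cost of EUR 800, a cost of about EUR 3,100 to 4,650 per responder becomes a negative ratio.

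The damage is confined to the cost-per-responder result with its ICER plane and acceptability curve. Within that result the conclusion would be inverted, so the rule must be corrected before the economic analysis is run.

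**What to change.** Amend the sentence in section 5.4 (CEA and CUA) so that treatment response is a decrease of at least 5 points from baseline on the PANSS negative subscale (N1-N7). State that change is scored so that improvement is positive wherever PANSS negative enters the economic evaluation: the responder rule, the ICER plane and the effect term E in INBRA. It would be sensible to name, in the same amendment, the assessment at which response is judged (end of treatment or 6-month follow-up), although that could equally be left to the analysis plan.

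The cost is a one-sentence amendment. It needs no new data and no change to the sample size or the primary analysis. Dating it before the economic analysis avoids any suggestion that the responder rule was turned round after the results were seen.

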### **Study procedures**

After the participants have read and signed informed consent, and before treatment allocation, all patients will undergo a two hour during test battery carried out by an academic research assistant. Afterwards, participants will be asked to carry along an electronic device/ with an application with which participants are prompted by a beep at random intervals throughout the day (for a 6-day period) to report about their current experiences and withdrawal behaviour (see Experience Sampling Method (ESM; 9) table 1). The test battery will be repeated at the end of treatment, and 6-months post- treatment.

Patients allocated to the CBTsa condition will receive group sessions for 4 weeks, and 6-8 weeks weekly individual CBT sessions (see above).

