| Quality of Life          | EQ-5D-5L; 12                                                                                  | To assess (changes in) quality of life we will make use of the EuroQol (EQ-5D-5L).                                                                                                                                                                                                                                                                                                                                                                                                                                                                            |
| Global functioning       | Global Assessment of Functioning Scale (GAF [13]).                                            | This scale is rated on a scale from 1 to 100, for the current situation and for highest level in past year. 1 to 10, for example, signifies 'a persistent danger of severely hurting self or others (e.g., recurrent violence) OR persistent inability to maintain minimal personal hygiene OR serious suicidal act with clear expectation of death', whereas 91 to 100 on the other hand, stands                                                                                                                                                             |

|                                     |                                                                                        |                                                                                                                                                                                                                                                                                                                                                                                                                                                                                                                                                                                                                                  |

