**5.5 Other study parameters**

Substance abuse, and socio-demographic variables (e.g. age, gender, medication prescription) will be added to the model as possible confounders.

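### The cost-utility analysis names no adjustment of incremental QALYs for baseline EQ-5D utility, so it gives up precision that the collected data could provide

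*Protocol*

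**What the plan says.** Section 5.4 (CEA and CUA) derives QALYs from the Dutch EQ-5D tariff and then says: "The incremental cost-effectiveness ratio (ICER) will be computed to obtain the costs per treatment response and the costs per QALY gained". It continues: "Stochastic uncertainty will be handled using 2,500 non-parametric bootstraps and plotting the simulated ICERs on the ICER plane". An acceptability curve over several willingness-to-pay ceilings follows. The sensitivity analyses named in 5.4 for this evaluation concern cost drivers only.

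Table 1 lists the instrument: "To assess (changes in) quality of life we will make use of the EuroQol (EQ-5D-5L". The battery is given before allocation, and Study procedures adds: "The test battery will be repeated at the end of treatment, and 6-months post- treatment". A baseline utility will therefore be on file.

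The covariates named for analysis are in section 5.5: "Substance abuse, and socio-demographic variables (e.g. age, gender, medication prescription) will be added to the model as possible confounders". Baseline utility is not among them, and that sentence is not tied to the cost-utility analysis. Quality of life is also analysed by a mixed model (5.3 and 5.4), but that estimate is not linked to the cost-effectiveness ratio (ICER).

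**The concern.** If QALYs are computed as the area under each patient's utility curve, the baseline utility enters in two ways: directly, as the first point of the curve, and indirectly, because later utilities correlate with it. A chance difference between the arms at baseline then passes into the difference in QALYs. Randomisation is within centre and stratified by sex, and neither balances utility.

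The protocol's other economic outcomes are changes from baseline on the PANSS (treatment response in the CEA, the continuous effect in the net-benefit regression). The QALY is the one economic outcome whose described derivation takes no account of the starting level. At stake is the precision of the QALY increment, and with it the spread of the ICER plane and the shape of the acceptability curve, for a stated secondary objective.

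**Working it through.** **The plan's own figure.** In Anticipated Cost-Effectiveness, 0.66 × 0.172 × 0.5 = 0.05676, stated as 0.057; 800 / 0.057 = EUR 14,035.09. Both reproduce. This is a pre-trial estimate and is not needed for the precision result below.

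**Inputs from the protocol.** 56 per arm (2.4). Treatment is 4 weeks of groups plus 6-8 weeks of individual sessions, so 10-12 weeks (3.1). The last visit is 6 months after treatment. Groups start at most one month after baseline (6.2).

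**Assumptions, not in the protocol.** Area-under-the-curve (trapezoidal) QALYs; visits at 0, 12 and 38 weeks; the same utility SD at each visit; one correlation r between any two visits.

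**Weights.** With t1 = 12/52 = 0.231 and t2 = t1 + 0.5 = 0.731 years, w = (t1/2, t2/2, (t2 − t1)/2) = (0.115, 0.365, 0.250). The sum of squares is 0.209; the square of the sum is 0.534.

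**Formulas**, in units of the utility SD:
- Slope of QALY on baseline utility: b = 0.115 + r × (0.365 + 0.250)
- Variance of the QALY: v = (1 − r) × 0.209 + r × 0.534
- Share of variance removed by adjustment: b² / v

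| r | b | v | b²/v | SE ratio, √(1 − b²/v) |
|---|---|---|---|---|
| 0.3 | 0.300 | 0.307 | 29% | 0.84 |
| 0.4 | 0.362 | 0.339 | 39% | 0.78 |
| 0.5 | 0.423 | 0.372 | 48% | 0.72 |
| 0.6 | 0.485 | 0.404 | 58% | 0.65 |

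The SD cancels, so the variance reduction depends only on r and the visit times. With r = 0.5, moving the second visit to 10 weeks gives 46% (b = 0.394, v = 0.335). Moving it to 16 weeks, for a one-month wait before groups start, gives 51% (b = 0.481, v = 0.451).

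**Size of the carried imbalance.** This does need an SD. The SE of the baseline utility difference is SD × √(2/56), which is 0.038 for an assumed SD of 0.20. A one-SE baseline difference moves the QALY difference by b times that: 0.011, 0.016 and 0.018 for r = 0.3, 0.5 and 0.6. Over SD 0.15 to 0.30 at r = 0.5 the shift is 0.012 to 0.024, in either direction.

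**SE of the QALY difference**, SD 0.20, r = 0.5, 56 per arm: unadjusted 0.2 × √(2/56 × 0.372) = 0.023; adjusted 0.2 × √(2/56 × (0.372 − 0.179)) = 0.017.

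**The case against.** The strongest reply is that the protocol is silent; it does not prescribe an unadjusted analysis. It does not say how QALYs are formed, and covariates for incremental QALYs are often left to a later analysis plan, which is not at hand. That stands, and it keeps the point small. Still, 5.4 goes down to the number of bootstraps and the plots, and a reader who follows it literally computes a ratio of unadjusted mean differences.

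It is also right that randomisation makes the unadjusted difference unbiased and that the bootstrap properly carries baseline imbalance as sampling error. The case for adjustment is precision and the removal of a measured chance difference, not the correction of bias.

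A reader might infer something stronger: that a one-SE imbalance takes the cost per QALY from EUR 14,035 to the cut-off in "This is below the €20.000 cut-off, as a result of which the intervention may be considered costeffective". With the assumed SD of 0.20 and r = 0.5, 800 / (0.05676 − 0.016) is indeed about EUR 19,600. The documents do not support this as a result of the planned analysis, for three reasons:
- EUR 14,035 counts intervention cost only, while the planned evaluation is societal with four cost types.
- The EUR 20,000 line appears only in the pre-trial estimate; the planned analysis uses a range of ceilings.
- Adjustment would not prevent it: one adjusted SE of 0.0166 gives 800 / (0.05676 − 0.0166), about EUR 19,900.

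Nor can the gain be put as power, since 5.4 plans no significance test of the QALY difference in the economic evaluation.

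**Conclusion.** The point holds as a minor one: a better estimator is available from data already planned, and the protocol does not name it. Nothing is stated wrongly or contradicted. Under area-under-the-curve QALYs, visits at 0, 12 and 38 weeks and equal correlations of 0.3 to 0.6, adjustment cuts the variance of the QALY difference by about 29% to 58%, which is a standard error 16% to 35% smaller. The reduction would be smaller if utilities correlate more weakly over time. The euro figures above are illustrative only. Cost-effectiveness is a secondary aim that the protocol sets out to explore, so no primary conclusion is affected.

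**What to change.** In section 5.4 (CEA and CUA), state that incremental QALYs are estimated by regressing each patient's QALY on treatment arm and baseline EQ-5D utility. Refit that regression in each of the 2,500 bootstrap samples, jointly with the cost difference so that the correlation between costs and effects is kept. Use the adjusted increments for the ICER, the ICER plane and the acceptability curve, and report the unadjusted result as a sensitivity analysis. Fixing this in advance also avoids a choice between two ratios once the data are seen.

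The cost is a sentence or two of wording and one extra regression per bootstrap sample. No new data, visits or patients are needed.
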